## 12 Study Procedures

See the Appendix for the schedule of events.

| Phase       | Time                                                                                                         | Description                                                                                                                                                                                                                                                                                                                                                      |
|-------------|--------------------------------------------------------------------------------------------------------------|------------------------------------------------------------------------------------------------------------------------------------------------------------------------------------------------------------------------------------------------------------------------------------------------------------------------------------------------------------------|
| Recruitment | 
Begin: January 2025
 
End: When n = 90 is reached (n = 60 intervention; n = 30 waitlist control)
 | 
Opt-in: Potential participants learn about the study and contact the research team. Information is shared via
 
 
• Posters in the front of organizations NGOs active in migration, health centers and community mental health centers, shelters, schools
 
• Flyers available at these institutions
 
 |

|                                                          |                                                                                                                                                                      |                                                                                                                                                                                                                                                                                                                                                                                                                                                                                                                                                                                                            |
|----------------------------------------------------------|----------------------------------------------------------------------------------------------------------------------------------------------------------------------|------------------------------------------------------------------------------------------------------------------------------------------------------------------------------------------------------------------------------------------------------------------------------------------------------------------------------------------------------------------------------------------------------------------------------------------------------------------------------------------------------------------------------------------------------------------------------------------------------------|
|                                                          |                                                                                                                                                                      | 
 
Flyers handed out at community events organized by NGOs active in migration
 
Posts will be published in the social networks of NGOs active in migration
 
 
Opt-out: NGOs that offer mental health services to Venezuelan migrants identify potential eligible subject, who - due to a lack of resources - could not be offered support by the NGO. Organizations directly reach out to these individuals to provide information about the study and give them the opportunity to learn more by a follow-up call by the research team or not.
 |
| Screening Consent                                        | Begin: January 2025 and as potential participants contact research team until n = 90 is reached.                                                                     | A call will be scheduled to present the information on the screening procedure, clarify doubts and verify comprehension. Electronic consent will be collected via REDCap or DocuSign.                                                                                                                                                                                                                                                                                                                                                                                                                      |
| Screening/baseline                                       | Begin: January 2025 and as potential participants contact research team until n =                                                                                    | Remotely via REDCap secure link (PHQ9, GAD7, PCL5, LEC5, demographics, exclusion criteria).                                                                                                                                                                                                                                                                                                                                                                                                                                                                                                                |
| Participation consent and enrollment                     | Begin: January 2025 and as potential participants contact research team until n = 90 is reached                                                                      | A link to the consent form will be sent via WhatsApp. A call will be scheduled to present the information on the study, clarify doubts and verify comprehension. Electronic consent will be collected via REDCap or DocuSign.                                                                                                                                                                                                                                                                                                                                                                              |
| Randomization and communication on begin of intervention |                                                                                                                                                                      | Remotely via telephone call
Demographics form via REDCap secure link
IPL via REDCap secure link                                                                                                                                                                                                                                                                                                                                                                                                                                                                                                      |
| Session 1 (Orientation session)                          | 
First group of 30 participants:
February 2025
 
Second group of 30 participants:
May 2025
 
Third group of 30 participants:
August 2025
 | 
Individually with provider
Remotely via Meet or WhatsApp videocall
60 min duration
 
Focus on getting to know each other, goal-setting, session scheduling, rules for cancellation and re-scheduling.
                                                                                                                                                                                                                                                                                                                                                                                  |
| Sessions 2 to 6                                          | 
First group of 30 participants:
February 2025
-May 2025
 
Second group of 30 participants:
                                                       | 
Individually with provider
Remotely via Meet or WhatsApp videocall 60 min duration
 
Focus on symptom relief (depression, anxiety and/or PTSD)
                                                                                                                                                                                                                                                                                                                                                                                                                                             |

|                                     |                                                                                                                                                                                            |                                                                                                                                                                                                                   |
|-------------------------------------|--------------------------------------------------------------------------------------------------------------------------------------------------------------------------------------------|-------------------------------------------------------------------------------------------------------------------------------------------------------------------------------------------------------------------|
|                                     | May-August 2025

Third group of 30 participants:
August -November 2025                                                                                                            |                                                                                                                                                                                                                   |
| Sessions 7 to 12                    | First group of 30 participants:
May - August 2025

Second group of 30 participants:
August-November 2025

Third group of 30 participants:
November 2025-February 2026 | Individually with provider
Remotely via Meet or WhatsApp videocall
60 min duration
Focus on other aspects relevant to mental health (emotional regulation, problem solving, adaptation related distress) |
| Assessments throughout intervention | January 2025 to February 2026                                                                                                                                                              | Remotely via REDCap secure link (PCL5 every week before the session, PHQ9 and GAD7 every 2 weeks before the session, acceptability and adherence every week after each session)                                   |
| Endline                             | May 2025 to February 2026                                                                                                                                                                  | Remotely via REDCap secure link (PHQ9, GAD7, LEC5 and PCL5)
12 weeks after first session in intervention group (or within 14 days of completion).
12 weeks after baseline in waitlist control group.        |
| Assessment at 1-month follow-up     | August 2025 to January 2026                                                                                                                                                                | Remotely via REDCap secure link (PHQ9, GAD7, LEC5, PCL5) one month after endline (or a maximum of a month later).                                                                                                 |
| Assessment at 3-month follow-up     | October 2025 to March 2026                                                                                                                                                                 | Remotely via REDCap secure link (PHQ9, GAD7, LEC5, PCL5) three months after endline (or a maximum of a month later).                                                                                              |
| Assessment at 6-month follow-up     | January to June 2026                                                                                                                                                                       | Remotely via REDCap secure link (PHQ9, GAD7, LEC5, PCL5) 6 months after endline (or a maximum of a month later).                                                                                                  |
| Data Analysis                       | June 2026 to July 2027                                                                                                                                                                     | Data analysis will take place using data analytic software and be used for publication and dissemination in scholarly journals and conferences.                                                                   |

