| Design/Methodology:             | 
Migrants will be randomized to receive the intervention (<math>n = 60</math>) or wait list control (<math>n = 30</math>). Mental health outcomes (PHQ9, GAD7, PCL5) will be assessed at baseline during screening, throughout the intervention, post treatment, and at 1-, 3-, and 6- months follow-up. Demographic information, the IPL will be assessed at the time of enrollment. LEC5 will be assessed at baseline and at 1-, 3- and 6-month follow-up. Acceptability will be assessed after each session. All assessments will be conducted by the research team through a secure link in REDCap. Each migrant will participate in 5 assessment sessions and 6-12 intervention sessions with prior assessment of mental health outcomes. The intervention sessions have a frequency of once a week. In the case of the waitlist control, mental health outcomes will be assessed at baseline at the time of enrollment and at endline 12 weeks after baseline. Once the endline has been assessed, they will receive the intervention, with corresponding assessments as described previously. In the case of the providers, feasibility and acceptability will be assessed after each session. See Appendix for a graph of the design, schedule and assessments.
 |

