## 4.2 Study Outcome Measures

### 4.2.1 Primary Outcome Measures

Since the intervention is transdiagnostic and addresses several CMD, there will be three primary outcome measures. Changes in anxiety will be measured using the GAD7 scale. This is a 7-item instrument that measures generalized anxiety. Changes in depression will be assessed using the PHQ9 questionnaire, which is a 9-item instrument that measures depression. Both instruments have been chosen because they are short, easy to administer and have been widely used in research. Spanish versions of GAD7 and PHQ9 have been validated and used in Venezuelan and Peruvian populations. Furthermore, prior studies with this same population conducted by the main researcher have used these instruments. Regarding PTSD, changes will be measured using the PCL5 checklist which has been validated for its use in Spanish-speaking populations and utilized in research projects with similar populations. The LEC5, which identifies potentially traumatic events in the life course of the participants, will be used at baseline and in the follow-up assessments along with the PCL5.

The primary outcomes will be measured at baseline during screening and at endline 12 weeks after baseline in the case of waitlist control. In the intervention group, they will be assessed at baseline during screening, weekly (PCL5) or every two weeks (PHQ9 and GAD7) throughout the intervention before the next session, after the last session of the intervention and at 1-, 3-, and 6-month follow-ups after completion of the intervention. Participants will be sent a secure REDCap link, where they will be asked to answer each item of the instruments.

See appendix with the English and Spanish versions of the instruments.

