## 6 Potential Risks and Benefits

### 6.1 Risks

It is unlikely that participants will be at risk of physical harm as a result of the study participation. The primary risks to participants are breach of confidentiality, fatigue or personal discomfort during the intervention sessions or assessments. Participants may find some of the topics addressed during the sessions or some of the questions asked during assessments to be emotionally upsetting and may experience short-term elevations in negative affect during active intervention sessions. As with any study of participants with mental illness, there is always the risk of symptom worsening. The weekly assessment of symptoms throughout the intervention will allow us to closely monitor any changes in the migrant participants and put in action a safety plan, in case of increased severity or suicidality. Weekly meetings with supervisors, who will be closely accompanied by the research team in weekly group meetings, will enable us to timely identify participants whose symptoms are not progressing as expected and to take timely action. At any point in the study if participants exhibit increasing severity of psychiatric symptoms that warrants a higher level of care, they will be referred to the local hospital. If symptoms require immediate medical management, participants’ family members will be contacted and recommended to bring the participant to the hospital emergency room.

Adaptation and assessment of a common element treatment protocol designed to improve mental health in forcibly displaced populations

Version 1, September 17, 2024

Furthermore, participants will be advised to call the hotline 113 to get in touch with counselors from the Peruvian mental health system or the number 106 in case they need an ambulance.

In the case of the provider participants, they may find some of the topics addressed during the sessions to be emotionally upsetting or may experience concern regarding the wellbeing of some participants. As mentioned above, frequent meetings with supervisors, closely accompanied by the research team, will enable us to discuss these concerns, to identify if the symptoms of a participant are not progressing as expected and to take timely action. Also, supervisions will provide with the opportunity to tackle the discomfort that a provider might be experiencing and to find means to alleviate it.

Other measure to be taken to protect the participants against risk are the following:

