### 7.2 Subject Exclusion Criteria

Participants with suicidality, homicidality and psychosis will be excluded from the study. An individual is excluded from the study if they endorse suicidal or homicidal thoughts in the past

Adaptation and assessment of a common element treatment protocol designed to improve mental health in forcibly displaced populations  
Version 1, September 17, 2024  
three months, or a lifetime psychosis diagnosis:

- Suicidal ideation: “When someone feels as upset as you do, they may have thoughts that life isn’t worth living. What thoughts have you had like this? Have you had these thoughts in the past three months?”
- Homicidal ideation: “When someone feels as upset as you do, they may have thoughts about hurting the person who has upset or hurt them. What thoughts have you had like this? Have you had these thoughts in the past three months?”
- Psychosis: “Do you have a diagnosis of psychosis or schizophrenia?”

If an individual endorses one of these items they will be referred to relevant care options.

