Once this information has been delivered and questions have been clarified, we will collect informed consent for the screening. To this end, participants will receive a secure link to REDCap. Upon consent, participants will be asked questions regarding age, nationality, date of arrival to Peru, suicidality, homicidality, psychosis and the items of the PHQ9, GAD7, LEC5 and PCL5. The researcher will walk the person through the questionnaires during the call, read the questions and mark their answers. If no exclusion and all inclusion criteria apply, individuals will receive a message inviting them to participate in the study. Otherwise, they will be communicated that they cannot be included in the study and information on organizations offering mental health support will be shared with them. If suicidality or homicidality is identified, a safety plan will be implemented. Individuals will be told that their safety is at risk and that we need to contact family member. We will contact a family member and refer to the hospital or other relevant care options, such as the Community Mental Health Centers. Furthermore, individuals will be advised to call the hotline 113 to get in touch with counselors from the Peruvian mental health system.

The Screening Consent Form is attached to this Protocol in a separate document.

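### In the visible text the suicidal and homicidal thought questions are asked only at screening, with no required check before waitlist participants start lay-delivered treatment at least 84 days later

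*Protocol*

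**What the plan says.** Section 7.2 excludes anyone who endorses suicidal or homicidal thoughts. Each question ends with the same look-back: "Have you had these thoughts in the past three months". Anyone who endorses one is referred to care.

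Section 10 places these questions in the screening call: "Upon consent, participants will be asked questions regarding age, nationality, date of arrival to Peru, suicidality, homicidality, psychosis", followed by the symptom scales. A researcher reads the questions and records the answers. The same section adds: "If suicidality or homicidality is identified, a safety plan will be implemented".

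The Section 12 table agrees. Its Screening/baseline row reads "Remotely via REDCap secure link (PHQ9, GAD7, PCL5, LEC5, demographics, exclusion criteria)". The Endline row reads "Remotely via REDCap secure link (PHQ9, GAD7, LEC5 and PCL5)", and the exclusion criteria are not in it. They are also absent from the rows for randomization, the sessions, the assessments during treatment and the follow-ups.

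On timing, Section 4.2.1 says: "The primary outcomes will be measured at baseline during screening and at endline 12 weeks after baseline in the case of waitlist control". The Protocol Summary then moves the waitlist arm into treatment: "Once the endline has been assessed, they will receive the intervention, with corresponding assessments as described previously".

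**The concern.** The protocol treats suicidal or homicidal thoughts in the last three months as a reason not to begin this lay-delivered treatment and to refer instead. For the waitlist arm, the design itself puts about that length of time between the answer and the first session. A participant who develops such thoughts while waiting would have been excluded and referred had they been present at screening. As scheduled in the visible text, that person can reach session 1 without being asked again.

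The moment matters because the treatment can include exposure to memories (Section 8), and Section 6.3 accepts that distress may rise at first. What is at stake is the safety of individual participants, not the estimate of the treatment effect.

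**Working it through.** No sample size, power or alpha figure is involved. The check compares places in the protocol and counts days.

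**Inputs**
- Waitlist arm: 30 of 90 randomised (Protocol Summary; Section 15.2).
- Baseline for the waitlist: at screening (Sections 4.2.1 and 5).
- Waitlist endline: 12 weeks after baseline (Section 12).
- Start of waitlist treatment: after endline (Protocol Summary).
- Look-back of the two questions: three months, taken as 90 to 92 days (Section 7.2).

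**Time from last answer to first session**
- Minimum gap = 12 weeks × 7 days = 84 days.
- The screening answers describe the three months before screening, so they cover 0 of those 84 days.
- If session 1 followed immediately, 84 of the preceding 90 to 92 days would be unasked. Any delay after endline lengthens the gap.

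**What is scheduled for the waitlist arm, step by step**

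| Step | Content in the visible text | Section 7.2 questions? |
|---|---|---|
| Screening/baseline | PHQ9, GAD7, PCL5, LEC5, demographics, exclusion criteria | Yes, read out by staff |
| Randomization | Call, demographics form, IPL | Not listed |
| Waiting period | No outcome assessment between baseline and endline | Not listed |
| Endline, week 12 | PHQ9, GAD7, LEC5, PCL5 by REDCap link | Not listed |
| Before sessions | Symptom questionnaires by REDCap link | Not listed |
| Session 1 | Getting acquainted, goals, scheduling; Section 8 adds exploring present difficulties | Not listed |

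**What could stand in for the questions**
- *Suicidal thoughts.* The endline PHQ9 precedes session 1, and the reference list includes a study in Lima that used the PHQ9 to assess suicidal ideation. It may therefore pick such thoughts up. The visible text does not say that anyone must read the endline PHQ9 before session 1, or what result would prompt action.
- *Homicidal thoughts.* No listed instrument is described as covering them. Detection would depend on the participant raising the subject or on someone noticing.

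**Would the repeat cover the wait?** A three-month look-back asked at day 84 reaches back 90 to 92 days, which is past screening. It covers the whole wait as long as the call falls no later than about day 90.

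**The case against.** The strongest reply is that nothing here is an error. Section 7.2 sets entry criteria, which are applied at entry; enrolled participants then fall under monitoring and referral. The intervention arm is not asked the two questions again either. That stands. It is why this is a recommended improvement and not a correction.

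The safeguards are also real:
- Section 6.1 provides for referral to the local hospital, and its wording covers the wait: "At any point in the study if participants exhibit increasing severity of psychiatric symptoms that warrants a higher level of care".
- Section 8 and the Protocol Summary send questionnaires before each session, and the waitlist receives them once treated.
- Section 8 has the orientation session explore present difficulties and sets up a referral network that expressly includes suicidality and homicidality.
- Section 13 has staff trained to recognise suicidal ideation, with weekly safety meetings; Section 14.2 adds routine data review.

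These narrow the gap considerably for suicidality, and it would be wrong to infer that the waitlist arm has no protection. What survives is limited. None of these is a required check tied to the start of treatment. Much of the monitoring runs during treatment, and referral follows only once someone has noticed a problem.

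The Appendix, with the schedule of events and the forms, and the provider manual are not shown. A repeat may be specified there, so a reader should not infer that the trial as a whole lacks one.

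Finally, a check can delay treatment for people who have already waited 12 weeks and have little other care. That is a genuine cost, and it argues for a prompt clinical decision rather than an automatic bar.

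**Conclusion.** The point holds in a limited form. In the body text and the Section 12 table, the two questions are asked once, at screening. All 30 waitlist participants start lay-delivered treatment at least 84 days later with no required risk check at that point. The residual gap is the absence of any required review of the endline PHQ9 and of any described question on homicidal thoughts.

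Two stronger readings are not supported. One is that starting these participants breaches eligibility: the protocol nowhere says Section 7.2 must be met again. The other is that the randomised comparison is affected: the waitlist's control measurement is taken at endline, before treatment starts, and nothing in the documents points to a statistical effect.

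The figures describe arm size and schedule, not risk. The documents give no rate of new suicidal or homicidal thoughts during the wait, so no number of affected participants can be stated. The conclusion assumes that the Appendix does not already contain the check.

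**What to change.** For the waitlist arm, add one step between endline and session 1, stated in the Section 12 table and in Section 9.1.2:

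1. Once the endline PHQ9, GAD7, LEC5 and PCL5 have been submitted, trained research staff review the PHQ9.
2. On the reminder call that Section 9.1.2 already schedules for the day before each session, staff repeat the two Section 7.2 questions on suicidal and homicidal thoughts before session 1. The psychosis question asks about a diagnosis and is not part of this point.
3. A positive answer triggers the Section 10 safety plan and prompt review by the principal investigator or a supervising clinician. That person decides whether session 1 goes ahead, is delayed or is replaced by referral.
4. The participant stays in the intent-to-treat analysis (Section 5), and all endline data are kept.

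The order matters. Asking only after the endline measures are in means the extra contact cannot influence the waitlist's only post-baseline control measurement.

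The cost is a few minutes of staff time for each of 30 people, and a short delay or a referral for some who have already waited 12 weeks. No new visit or instrument is needed. If the Appendix already contains the check, a one-line cross-reference in the Endline row is enough.
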